# Evaluating Diuretics in Normal Care (EVIDENCE): protocol of a cluster randomised controlled equivalence trial of prescribing policy to compare the effectiveness of thiazide-type diuretics in hypertension

**DOI:** 10.1186/s13063-021-05782-9

**Published:** 2021-11-17

**Keywords:** Medical record linkage, Comparative effectiveness research, Drug prescriptions, Primary health care, Hypertension

## Abstract

**Introduction:**

Healthcare systems must use treatments that are effective and safe. Regulators licensed many currently used older medications before introducing the stringent evidential requirements imposed on modern treatments. Also, there has been little encouragement to carry out within-class, head-to-head comparisons of licensed medicines. For commonly prescribed drugs, even small differences in effectiveness or safety could have significant public health implications. However, conventional clinical trials that randomise individual subjects are costly and unwieldy. Such trials are also often criticised as having low external validity. We describe an approach to rapidly generate externally valid evidence of comparative safety and effectiveness using the example of two widely used diuretics for the management of hypertension.

**Methods and analysis:**

The EVIDENCE (Evaluating Diuretics in Normal Care) study has a prospective, cluster-randomised, open-label, blinded end-point design. By randomising prescribing policy in primary care practices, the study compares the safety and effectiveness of commonly used diuretics in treating hypertension. Participating practices are randomised 1:1 to a policy of prescribing either indapamide or bendroflumethiazide when clinically indicated. Suitable patients who are not already taking the policy diuretic are switched accordingly. All patients taking the study medications are written to explaining the rationale for changing the prescribing policy and notifying them they can opt-out of any switch. The prescribing policies’ effectiveness and safety will be compared using rates of major adverse cardiovascular events (hospitalisation with myocardial infarction, heart failure or stroke or cardiovascular death), routinely collected in national healthcare administrative datasets. The study will seek to recruit 250 practices to provide a study population of approximately 50,000 individuals with a mean follow-up time of two years. A primary intention-to-treat time-to-event analysis will be used to estimate the relative effect of the two policies.

**Ethics and dissemination:**

EVIDENCE has been approved by the East of Scotland Research Ethics Service (17/ES/0016, current approved protocol version 5, 26 August 2021). The results will be disseminated widely in peer reviewed journals, guideline committees, National Health Service (NHS) organisations and patient groups.

**Trial registration:**

ISRCTN46635087. Registered on 11 August 2017 (pre-recruitment).

## Background

Formal comparisons of the effectiveness and safety of medicines with similar modes of action and indication are rare [1]. As the number of available medicines increases, high-quality evidence of comparative effectiveness becomes increasingly essential. This problem was the subject of two recent Lancet reviews and accompanying commentary that promoted comparative effectiveness research for public health [2–4].

Randomised placebo-controlled trials (RCTs), often considered the gold standard for generating healthcare evidence, can be cumbersome, expensive and time-consuming [5]. Such trials often have low external validity because trial participants are likely to differ from patients encountered in usual healthcare practice [6]. As it is conventionally conducted, the randomised controlled trial is not a suitable tool for generating comparative effectiveness evidence at the required scale and speed. A more efficient method that can generate evidence within acceptable boundaries of precision and within reasonable time frames and resources is needed.

The potential for using routinely collected data to generate knowledge within a learning healthcare framework is increasingly recognised [7]. Whilst such data can be used to produce evidence quickly and efficiently, non-interventional research is subject to biases that limit its usefulness for clinical decision making [8]. The result is, despite significant advances in causal inference techniques [9, 10], purely observational research often fails to influence policy and behaviour [8]. Researchers can enhance the value of these large datasets by combining them with the essential features of randomised trials and healthcare system-specific processes.

We describe a study design that uses routinely collected healthcare data in combination with cluster randomisation to generate high-quality evidence of comparative effectiveness of prescribing policy efficiently and rapidly. Using the example of thiazide-type diuretic medications, widely used for managing hypertension, the EVIDENCE (EValuatIng DiurEtics in Normal CarE) study will compare policies for prescribing indapamide or bendroflumethiazide. Previous work by our group has demonstrated good public support for this type of research [11]. Whilst we have developed the EVIDENCE protocol using the exemplar of diuretic medicines, the infrastructure and methodology will be applicable to the wide range of situations where comparative safety and effectiveness evidence is lacking for treatments commonly used in the NHS.

### Rationale for EVIDENCE

Cardiovascular diseases are the leading cause of death worldwide with high blood pressure being the most common preventable cause, responsible for 54% of strokes and 47% of ischaemic heart disease [12]. Given the high prevalence of hypertension, affecting around 12.5 million people in England in 2015 [13], even slight differences in the effectiveness or safety between widely prescribed blood pressure-lowering medications would imply many thousands of potentially avoidable events.

Thiazide and thiazide-like diuretics are a cornerstone of hypertension treatment. The scant evidence for clinically relevant differences between the thiazide and thiazide-like diuretics has been interpreted variably by blood pressure management guidelines internationally [14]. In 2011, the UK NICE guidelines for managing hypertension [15] stated that “a thiazide-like diuretic, chlortalidone or indapamide, should be chosen in preference to a conventional thiazide diuretic such as bendroflumethiazide or hydrochlorothiazide”. The guidelines development group (GDG) conceded that “there were no direct comparisons between the different diuretics with regard to clinical outcomes” and that “the GDG found it difficult to reach firm conclusions regarding the comparative efficacy of different thiazide-type diuretics with regard to blood pressure-lowering” [15]. Before this guidance, UK diuretic use for hypertension was almost entirely restricted to bendroflumethiazide [16, 17]. The 2011 guideline was therefore suggesting a significant change to the prevalent prescribing of these drugs. The 2019 guideline update, NG136, still recommends a thiazide-like diuretic in preference to a conventional thiazide [18].

The interpretation of the evidence by the GDG has been disputed [19]. A recent meta-analysis from our group has further demonstrated the lack of evidence in this area [20]. Despite NICE guidance, bendroflumethiazide remains the dominant diuretic prescribed in the UK to treat hypertension [16]. The hypertension community remains in equipoise about diuretic choice, and many local prescribing policies did not take up the NICE recommendation. This situation is likely to have also been influenced by chlortalidone not being readily available in the UK and indapamide being significantly more expensive than bendroflumethiazide [21].

To conduct a conventional individually randomised clinical trial comparing the effects of bendroflumethiazide and indapamide on cardiovascular outcomes would be very challenging; such a trial would likely require the recruitment of over 50,000 individual patients, making it one of the largest hypertension trials ever. Furthermore, as both drugs are now off-patent, securing sufficient funding to achieve this level of recruitment for this comparison and many others within current health research funding structures would be a formidable task. Therefore, we propose the EVIDENCE trial design as a pragmatic solution to the problem of how to conduct comparative effectiveness research within existing constraints.

### Objectives

The primary objective of EVIDENCE is to estimate the relative effectiveness of two prescribing policies for the management of hypertension in terms of both safety and efficacy. If study results suggest that there is no clinically relevant difference [22], this will justify individual prescribers and healthcare providers continuing to decide which drug to offer based on other relevant factors such as availability and price.

Our secondary objective is to evaluate the feasibility of the EVIDENCE method for conducting clinical effectiveness research in the NHS. We intend that this methodology be adapted to many disease areas as part of a future learning NHS.

## Methods and analysis

### Study design

EVIDENCE is a cluster-randomised, prospective, parallel-group, blinded outcome study comparing cardiovascular event rates in patients in general practices being prescribed either bendroflumethiazide or indapamide to manage hypertension.

The cluster randomised approach has been chosen to increase the feasibility of performing comparative effectiveness research at scale in the NHS; the cost of conducting multiple comparisons of commonly used medicines using individual patient recruitment and randomisation would be prohibitive. However, this feasibility advantage must be balanced against a need for careful statistical planning [23, 24].

There is, nonetheless, an important advantage of cluster randomisation without individual opt-in consent over more traditional approaches: using an opt-out of intervention approach is likely to result in a study cohort far more representative of the intended patient population [25, 26].

NHS general medical practices using electronic medical records will be invited to take part in the study. The study will recruit practices from a broad range of NHS trusts, including remote and rural practices that are often excluded from traditional trial participation. The study is designed to be minimally disruptive to practice workflow and uses routine prescribing activities. Recruitment of general practices and randomisation of prescribing policy at the practice level allows the rapid accrual of a large observational study population whilst incorporating the statistical benefits of randomisation. Routinely collected national datasets of hospitalisations and deaths will be used to compare cardiovascular event rates between individuals being treated under each of the two policies. National dispensed prescribing information will be used to facilitate the definition of analysis cohorts. General practice data will be used to gather evidence on potentially important adverse effects such as electrolyte and metabolic disturbances. The study will take place in Scotland where national datasets are well established, although we anticipate that extension to other regions of the UK would be feasible. Figure 1 shows the EVIDENCE study flow diagram.

**Fig. 1 Fig1:**
[figure not shown]
EVIDENCE study flow diagram

### Identification of the study population

A search will be performed in each recruited practice using a bespoke EHR-specific tool to identify patients who may be subject to a medication switch after policy randomisation based on the following criteria.

#### Inclusion criteria

Documented diagnosis of hypertension (on practice hypertension register)Currently receiving repeat prescriptions for bendroflumethiazide or indapamideAged over 18

#### Exclusion criteria

Documented history of an adverse drug reaction to either medicationHistory of having been prescribed both thiazide-like diuretics at different times, indicating a potential clinical reason for not being able to take one or otherOther cogent clinical or other indication for not switching medication (see below)

A draft list of potential patients identified in each practice will be provided to a relevant member of the primary care team (a practice GP or delegate) for approval. Approval will include the redaction of any individuals considered not suitable for the drug switch, based on local knowledge. The approved list will be used for the study and represents the study population for the practice.

### Cluster randomisation

The randomisation unit in this study is the practice (the cluster); patients are not individually recruited. Following identification and approval of the practice study population, the practice will be randomised using an online study portal. Randomisation will be 1:1, block balanced by practice list size, using a computerised randomisation algorithm. Block sizes are randomly allocated to prevent staff implementing the trial from guessing the next allocation. The prescribing policies will be applied at a practice level, and individual prescribers will remain free to prescribe as clinically appropriate.

## Intervention

### Policy medications

Bendroflumethiazide is licensed for the treatment of hypertension and oedema, although by far the most common indication is hypertension. The typical dose for hypertension is 2.5 mg once daily. A small minority of patients are prescribed 5 mg or 1.25 mg daily.Indapamide is licensed to treat hypertension only at 2.5 mg/day, although tablets are scored and 1.25 mg can be taken. It is also available as a more expensive slow-release preparation at a dose of 1.5 mg. The 2.5 mg standard release formulation will be used in this study.

### Policy implementation

#### Informing patients about the study

Immediately following randomisation of a practice, all patients in the study population will be written to informing them that their practice is taking part in the EVIDENCE study. The letter will be printed on practice-specific headed paper and will briefly explain why the study is being conducted. It will also advise that the patient's repeat prescriptions for thiazide-type medication may be switched in line with the newly assigned practice prescribing policy. The letter directs patients who may have any questions, concerns, or objections to visit a study-specific website (www.memoresearch.com/evidence) or directly contact the study team. The study team will provide further information and, if the patient confirms that they would prefer to opt-out of any switch and remain on their current medication, the study team will not action the switch for that individual.

#### Repeat prescription switching

Patients whose current medication prescription is concordant with the randomly assigned policy will remain on their existing strength and dosage of thiazide-type diuretic. Where a patient is not being prescribed for in concordance with the randomly assigned policy, future repeat prescriptions will be altered as follows:
Bendroflumethiazide 2.5 mg or 5 mg will be changed to indapamide (standard release) 2.5 mg.Indapamide 2.5 mg will be changed to bendroflumethiazide 2.5 mg.Indapamide 1.5 mg (modified release) will be changed to bendroflumethiazide 2.5 mg.

Practices assigned to indapamide will also be offered the choice of having any existing indapamide 1.5 mg modified release prescriptions switched to the more cost-effective 2.5 mg version, in keeping with the NICE guidelines.

The study pharmacist/technician will facilitate any prescription changes using established practice prescribing management procedures. All procedures for implementing switches are specified in a study Operations Manual. After the initial switching phase, all patients who newly require a thiazide-type diuretic for hypertension will be subject to the randomly assigned policy. Where possible, integrated electronic practice formularies will be updated to remind prescribers of the policy when issuing new prescriptions for thiazide/thiazide-like diuretics.

### Patient and public involvement

During the study pilot, feedback on study materials and methods was sought from patients and healthcare staff who contacted the study team. This feedback was incorporated into improved patient letters and switching methods. Our research unit’s public involvement group have discussed the research proposal and design, providing essential guidance on preferred patient communication methods. A study-specific patient involvement group will be formed to advise the study management group on ongoing patient communications and dissemination.

### Outcomes

Primary and secondary outcomes will be determined at an individual level and identified by individual-level record linkage of practice study populations to de-identified NHS datasets.

#### Primary outcome

MACE (major adverse cardiac event) is a widely accepted composite end-point employed for hypertension trials [27]. For this study, we define MACE as a hospitalisation for myocardial infarction, coronary revascularisation, stroke or heart failure, or vascular death.

#### Secondary outcomes

Individual components of the primary outcomeAll-cause mortalityMetabolic complications (hypokalaemia and hyponatraemia)New diabetes mellitus diagnoses

#### Tertiary outcomes

We will evaluate the method in terms of practice workload and acceptability, subsequent prescribing patterns, and treatment escalation.

### NHS data sets

These data will be provided by the electronic Data Research and Innovation Service (eDRIS), a part of Public Health Scotland. Permission to do this has been obtained from the Public Benefit and Privacy Panel for Health and Social Care (HSC-PBPP). If practices in other parts of the UK are recruited, this information will be obtained through the relevant national agencies.

Dispensed prescribing data for participating practices will be linked to Scottish hospitalisation (SMR01) and National Records of Scotland (NRS) death registration datasets. General practice data will complement these national datasets and allow more accurate ascertainment of secondary outcomes.

All analyses will use anonymised data within a secure research environment, accredited under the NHS Digital - Data Security and Protection Toolkit and the eDRIS National Safe Haven.

#### Clinical adjudication of cardiovascular events

The use of routinely collected NHS data for determining cardiovascular end-points for clinical trials is practical and cost-effective. It has been used extensively for large pragmatic trials with careful adjudication of all end-points by a specialised clinical committee [28–31]. However, as administrative data improves, it seems increasingly feasible to use the data without formal adjudication [32, 33]. We intend to adjudicate a proportion of outcome events identified from administrative data to estimate the sensitivity and specificity of administrative diagnostic coding in the study population. This process will require de-anonymisation of the individuals experiencing these events for clinical record retrieval. We have established and standardised procedures to do this based on previous and ongoing trials [34].

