#### Sample size

EVIDENCE is a cluster randomised study; statistical power, therefore, depends on the number of practices, the mean number of patients in each practice and the event rate and their variability between practices. We used data obtained from the Clinical Practice Research Datalink for the Bendroflumethiazide versus Indapamide for Primary Hypertension: Observational (BISON) study to estimate these variables [36]. First, we identified patients similar to the expected EVIDENCE study population and found an average of 200 individuals per practice, but with substantial variation in numbers between practices (standard deviation 140). We then defined an arbitrary index date and calculated the incidence of the EVIDENCE composite endpoint following that date. The overall event rate was 0.0305 per patient-year (0.0265 in patients with no previous outcome event and about six times higher in the 7% of follow-up time for patients with an earlier event). Finally, we estimated the between-practice standard deviation to be 0.0047.

Using these parameters, we ran simulations using random samples of 250 practices (sample size 50,000) with a mean follow-up time of 2 years and clinically plausible relative risks between treatments of 1.1 to 1.2. We also allowed the possibility that the BISON study overestimated the event rate by a factor of 2 or 3. We fitted mixed-effects models, in which variation between practices was treated as a random effect, and prior history was treated as a patient-level fixed effect, to estimate the confidence interval for the relative risk between treatments. Finally, we conducted a 2-sided test of the superiority of one treatment over the other. Assuming event rates are close to those found in the BISON study, a study size of 50,000 individuals (250 practices) will have 80% power to detect a relative risk of about 1.12 between treatments. If the event rate is 2 or 3 times lower, this study will have 80% power to detect relative risks of 1.16 and 1.19, respectively.

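### Adjudicating only code-positive events estimates positive predictive value; it cannot deliver the sensitivity that the article promises, and gives specificity only as a derived bound

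*Protocol article*

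**What the plan says.** The section Clinical adjudication of cardiovascular events in the protocol article fixes three things.

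- The sample: "We intend to adjudicate a proportion of outcome events identified from administrative data to estimate the sensitivity and specificity of administrative diagnostic coding".
- The purpose: "to estimate the sensitivity and specificity of administrative diagnostic coding in the study population".
- Whose records are pulled: "This process will require de-anonymisation of the individuals experiencing these events for clinical record retrieval".

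Under NHS data sets, dispensed prescribing data are to be "linked to Scottish hospitalisation (SMR01) and National Records of Scotland (NRS) death registration datasets". The same section gives general practice records a supporting role: "General practice data will complement these national datasets and allow more accurate ascertainment of secondary outcomes". Nowhere does the article describe reviewing patients, admissions or deaths that carry no outcome code. It gives no number or proportion of events to be adjudicated, and no expected accuracy figure.

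**The concern.** The stated sample and the stated estimands do not match. Sensitivity asks what share of true events were coded, so it needs true events that were not coded. Specificity asks what share of non-events were left uncoded, so it needs patients without events. A sample drawn wholly from coded events contains neither, and reviewing more coded events does not change that.

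At stake is what the validation exercise can say. A confirmed proportion reported as sensitivity or specificity would be mislabelled, and would look like reassurance about missed events when none had been looked for. The Objectives section makes feasibility of the method a secondary objective and intends its reuse in other disease areas, so a mislabelled accuracy measure could be carried into later studies.

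**Working it through.** The article states no adjudication figure, so there is nothing to reproduce. The check is whether the promised quantities can be identified from the stated sample.

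**Inputs from the Sample size section.** "random samples of 250 practices (sample size 50,000) with a mean follow-up time of 2 years", and "The overall event rate was 0.0305 per patient-year".

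**Assumed, not in the article.** One event per patient; PPV of 0.80 to 0.95; 0% to 5% of unflagged patients with a missed event.

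**Step 1, definitions.** With TP, FP, FN and TN for true and false positives and negatives:

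- PPV = TP/(TP+FP)
- sensitivity = TP/(TP+FN)
- specificity = TN/(TN+FP)

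TP and FP come from flagged events; FN and TN come only from unflagged patients. Inside the planned sample FN = TN = 0 by design. A sensitivity computed there is 1 and a specificity is 0, whatever the coding is really like.

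**Step 2, totals.** Flagged: 50,000 × 2 × 0.0305 = 3,050. Unflagged: 50,000 − 3,050 = 46,950.

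**Step 3, PPV of 0.90.** TP = 0.90 × 3,050 = 2,745 and FP = 305. FN is the missed share × 46,950, and TN = 46,950 − FN.

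| Missed share of unflagged | FN | Sensitivity | Specificity |
|---|---|---|---|
| 0% | 0 | 1.00 | 0.9935 |
| 0.5% | 235 | 0.92 | 0.9935 |
| 1% | 470 | 0.85 | 0.9935 |
| 2% | 939 | 0.75 | 0.9934 |
| 5% | 2,348 | 0.54 | 0.9932 |

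Every row is compatible with the same adjudication result. At 5%, for example, 2,745/(2,745 + 2,348) = 0.54.

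**Step 4, other PPVs.** Over the same missed shares:

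- PPV 0.80: sensitivity 1.00 to 0.51, specificity 0.987 to 0.9865.
- PPV 0.95: sensitivity 1.00 to 0.55, specificity 0.9968 to 0.9966.

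Specificity hardly moves because the outcome is uncommon and the unflagged group is large. Sensitivity moves a great deal for the same reason: a small share of a large unflagged group is a large number of missed events.

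**Step 5, what PPV can inform.** Suppose a share f of reference-arm coded events is false, the false-positive rate is the same in both arms, and the true relative risk is 1.12. The observed ratio is (1 − f) × 1.12 + f, which is 1.114, 1.103 and 1.096 for assumed f of 5%, 14% and 20%. Multiplying the observed ratio by the ratio of the arms' PPVs undoes this. At f = 14% the reference PPV is 0.86 and the other arm's is 0.86 × 1.12/1.1032 = 0.873, and 1.1032 × 0.873/0.86 = 1.12. The planned sample can therefore supply what a false-positive correction needs, provided PPV is estimated by arm.

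**The case against.** Several points on the other side have force.

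- **Both measures are lost.** A reader might infer this, or that nothing but PPV can be learned. That goes too far. The study will know its flagged and unflagged totals, and with PPV these confine specificity to a narrow band. Confusion between components, such as infarction coded as heart failure, can also be examined, though only among events that were flagged.
- **The exercise is the justification for using unadjudicated codes.** A reader might infer this from the order of the sentences. The article does not say it: it rests that choice on improving administrative data and cited work, and the analysis section does not make the primary analysis depend on the adjudication.
- **The shrinkage of 1.12 towards 1 is the harm done by this error.** It is not. The shrinkage comes from false positives, which the planned sample can measure, and it would occur whatever the measure were called. What the sample cannot show is missed events. If these are unrelated to arm, they mainly cost precision and leave a relative risk for an uncommon outcome nearly unbiased; the article gives no basis for assuming that they differ by arm.
- **General practice data could reveal missed events.** The components of the primary outcome are listed as secondary outcomes, and general practice data are meant to help ascertain secondary outcomes. But the text does not connect those data to adjudication or to measuring coding accuracy.
- **The article condenses a fuller protocol and promises an analysis plan.** Either could describe a code-negative sample. That would excuse silence, but the article is not silent: it names a sample and an aim that do not fit each other.

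The first three limit the size of the point. The last two do not remove it.

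**Conclusion.** Wrong as written, with limited consequences. A code-positive sample directly estimates PPV. It leaves sensitivity unidentified, at 1.00 to 0.54 for an assumed PPV of 0.90 and an assumed missed share of 0% to 5%, and it gives specificity only through a derived bound of about 0.993.

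The numerical range rests on those assumptions, on one event per patient, and on the event rate in the Sample size section. That section allows the rate to be 2 or 3 times lower, which would widen the range for sensitivity: with 1,525 flagged patients, PPV 0.90 and a 5% missed share, TP = 1,372.5, FN = 0.05 × 48,475 = 2,424 and sensitivity = 0.36. The conclusion that sensitivity is unidentified needs none of these assumptions; it follows from the stated sample.

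The primary analysis and the sample size are untouched, and the text does not support a claim that the primary result is biased because of this wording. The consequence is an invalid validation claim, in particular about missed events.

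**What to change.** 1. Restate the aim as estimating the PPV of each coded component of the primary outcome, overall and by randomised arm.
2. Draw the adjudicated events as a random sample of flagged events, stratified by arm and component.
3. Report specificity only as a bound derived from PPV and the flagged and unflagged totals, and drop the claim to sensitivity.
4. Add a sensitivity analysis of the relative effect corrected for PPV, with the uncertainty in PPV carried through. In the worked case the two arms' PPVs differ by only 0.013, so a small sample would make an arm-specific correction imprecise, and the report should show this.

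The cost is a more modest validation claim and a little more analysis; the number of records reviewed need not change.

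If the sponsor prefers to keep the sensitivity aim, a random sample of code-negative admissions and deaths must be added, for example those with other cardiovascular codes and those with non-cardiovascular codes, and analysed with weights for the sampling fractions. That brings extra record retrieval and review, and de-anonymisation would have to extend to people without a coded event.
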